There is evidence to suggest that males and females may respond differently to resistance exercise, with respect to muscle damage. For instance, some studies have shown greater and more sustained increases in blood markers of muscle damage and inflammation in males than females following resistance exercise (Amorim et al., 2014; Heavens et al., 2014). It has been speculated whether these differences are due to a protective effect of oestrogens (Enns & Tiidus, 2008; Peter M Tiidus, 2003). Therefore, not only is the muscle damage response to heavy vs. lighter resistance exercise inconsistent in males, but it cannot be determined whether females will respond in the same way. Thus, the first objective (part a) of this research is to compare the muscle damage response induced by an acute bout of high- or low- load resistance exercise between males and females.

Another strategy that has shown to reduce exercise-induced muscle damage is the consumption of dietary protein, either as a whole-food source (such as milk) or as a supplement (such as isolated whey protein). It is believed that protein, or rather the amino acids which make up protein, aid the repair or replacement of damaged muscle fibres, then promote growth of the new healthy fibres. Accordingly, research has shown that ingesting protein/amino acids before or after muscle-damaging exercise can alleviate muscle soreness, improve blood markers of muscle damage, and reduce the decline in maximal force and flexibility. In particular, studies have shown that consuming a ~20 g dose of milk protein immediately after (Cockburn et al., 2008) or for several times a day after (Draganidis et al., 2017) resistance exercise improved the recovery time of muscle soreness and maximum force, and also lowered levels of damage markers in the blood. However, these studies were conducted with male participants who were well-trained in resistance exercise. It is not yet known whether milk protein effectively reduces exercise-induced muscle damage in untrained females. Therefore, the second objective (part b) of this research is to investigate the impact of milk protein ingestion on exercise-induced muscle damage in untrained females.

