**A13. Please summarise your design and methodology. It should be clear exactly what will happen to the research participant, how many times and in what order. Please complete this section in language comprehensible to the lay person. Do not simply reproduce or refer to the protocol. Further guidance is available in the guidance notes.**

OBJECTIVE 1/PART A: This study will employ a randomised parallel groups design, for which 40 healthy participants (20 males and 20 females) aged 18-35 years will be recruited. Prior to the first laboratory visit, prospective participants will have the opportunity to ask questions and gain further information about the study via a video/phone call with the

lead researcher. If willing to participate, participants will be asked to electronically sign a consent form. Female participants will be asked to record their menstrual cycle and inform the lead researcher at the onset of menses – this information will be used to arrange the time of the baseline assessments, as all measures will be conducted during the late follicular phase of the menstrual cycle.

For the first visit, which acts as a familiarisation session, participants will arrive at the laboratory in the morning and be screened for eligibility with a standard health and readiness to exercise questionnaire. Next, participants will be familiarised with the exercise equipment and demonstrated correct form. Then, participants' maximal strength will be estimated through a one repetition maximum (1RM) test on the leg press and leg extension machines. Approximately three days later, participants will return to the laboratory and a baseline assessment of body composition will be conducted using dual energy X-ray absorptiometry (DXA). Two whole-body DXA scans will be conducted in each participant (one immediately following the other after repositioning) to allow for the precision of DXA to be measured. The 1RM test will be repeated on the leg press and leg extension machines for confirmation of maximal strength. Participants will then be randomly assigned to either a low-load (30% 1RM) or high-load (80% 1RM) exercise condition, such that each group will have an equal number of males and females.

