**A59. What is the sample size for the research? How many participants/samples/data records do you plan to study in**

*total? If there is more than one group, please give further details below.*

Total UK sample size: 62

Total international sample size (including UK):

Total in European Economic Area:

*Further details:*

PART A: 20 males and 20 females

PART B: 22 females

**A60. How was the sample size decided upon?** *If a formal sample size calculation was used, indicate how this was done, giving sufficient information to justify and reproduce the calculation.*

PART A: A statistical power analysis was conducted. It was determined that a sample size of 8 per group was required to have 80% power to detect a between-group difference in muscle strength of 14%, when using a dependent t-test with a 0.05 two-sided significance level. A ~20% drop-out is anticipated, therefore, 10 males and 10 females in both groups will be recruited (n = 40 total).

PART B: A statistical power analysis was conducted. It was determined that a sample size of 9 per group was required to have 80% power to detect a between-group difference in muscle strength of 13%, when using a dependent t-test with a 0.05 two-sided significance level. A ~20% drop-out is anticipated, therefore, a total of 22 females will be recruited.

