**A61. Will participants be allocated to groups at random?**

☒ Yes ☐ No

*If yes, please give details of the intended method of randomisation:*

With each eligible participant identified, a coin will be tossed to decide which group they go into.

**A62. Please describe the methods of analysis (statistical or other appropriate methods, e.g. for qualitative research) by which the data will be evaluated to meet the study objectives.**

PART A: The Shapiro Wilk test will be used to assess the distribution of the data and to ensure no assumptions for statistical models are violated. Any data that violate the assumptions will be logarithmically transformed before statistical analysis. A two-way mixed design analysis of variance (ANOVA) will be used to analyse each muscle damage marker between exercise conditions and within time points. A two-way between-subjects ANOVA will be used to analyse each muscle damage marker between exercise conditions and between sexes. Independent t tests with Bonferroni corrections will be used to compare time-points between exercise conditions for all measures. Paired t tests will be used to detect any significant within-group changes between time points.

PART B: The Shapiro Wilk test will be used to assess the distribution of the data and to ensure no assumptions for statistical models are violated. Any data that violate the assumptions will be logarithmically transformed before statistical analysis. A two-way mixed design ANOVA will be used to analyse each muscle damage marker between dietary conditions (protein or placebo) and within time points. Independent t tests with Bonferroni corrections will be used to compare time-points between dietary conditions for all measures. Paired t tests will be used to detect any significant within-group changes between time points.

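### In A62 Part A, the time-specific load comparisons leave out sex and no planned model holds load, sex and time together, which costs power where a marker differs by sex

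*Protocol*

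**What the plan says.** A62 of the protocol names three Part A analyses that compare loads.

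- A load-by-time analysis without sex: "A two-way mixed design analysis of variance (ANOVA) will be used to analyse each muscle damage marker between exercise conditions and within time points".
- Load and sex together in a between-subjects ANOVA for each marker, with no time factor.
- Comparisons at each time point, also without sex: "Independent t tests with Bonferroni corrections will be used to compare time-points between exercise conditions for all measures".

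A13 intends randomisation to the two loads "such that each group will have an equal number of males and females", and A60 plans 10 men and 10 women per load. A61 allocates by coin toss and mentions no stratification by sex. A12 cites studies that found "greater and more sustained increases in blood markers of muscle damage and inflammation in males than females", without giving a size. A57 defines the primary outcome as changes in damage markers caused by the exercise.

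**The concern.** When a design balances a factor across the groups, the analysis should normally carry that factor. If it does not, the spread between men and women counts as unexplained variation in the load comparison, even though balance has removed it from the difference between load means. The standard error is then too large, the interval too wide and a real load effect easier to miss. The protocol's own background gives reason to expect a sex difference in blood markers. Completers are few, about 8 per sex-by-load cell after the expected drop-out, so there is little power to spare.

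**Working it through.** **Inputs**

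- Alpha: "0.05 two-sided significance level" (A60).
- Cell size: 10 per sex-by-load cell recruited, about 8 after drop-out (A60).
- Marker SD and sex gap: not given. The within-sex SD is set to 1 and the gap s is assumed to run from 0 to 2 within-sex SDs.
- Load effect: set to give 80% power with load and sex in the model, which is 0.91 SD at 10 per cell and 1.025 SD at 8 per cell.

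**1. The plan's own figure.** A60 states "It was determined that a sample size of 8 per group was required" for "80% power to detect a between-group difference in muscle strength of 14" per cent, "when using a dependent t-test". The drop-out step reproduces: 8 / (1 − 0.20) = 10. The 8 cannot be checked, because no SD is stated. A paired test with n = 8 needs a standardised difference of 1.156, implying an SD of differences of 14 / 1.156 = 12.1 points. An independent test with 8 per group needs 1.507, implying an SD of 14 / 1.507 = 9.3 points. Neither gives the size of a sex gap.

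**2. Standard error of the pooled t test under equal sex numbers.** With half of each load group shifted by s, the shift adds N·s²/4 to the within-group sum of squares, which is divided by N − 2. The true variance of the difference in means does not change. So

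SE ratio = √(1 + (s²/4) · N/(N − 2)).

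With N = 40 and s = 1: √(1 + 0.25 × 40/38) = √1.263 = 1.12.

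**3. Type I error and power**, from 40,000 simulated trials per setting at 10 per cell. Power with sex modelled is about 80% throughout.

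| Sex gap (SD) | SE ratio | Type I error, pooled t (nominal 5%) | Power, pooled t, alpha 0.05 | Power, pooled t, alpha 0.05/6 |
|---|---|---|---|---|
| 0 | 1.00 | 5.0% | 80% | 80% |
| 0.2 | 1.005 | 4.8% | 80% | 80% |
| 0.5 | 1.03 | 4.4% | 78% | 77% |
| 1 | 1.12 | 2.8% | 73% | 70% |
| 1.5 | 1.26 | 1.3% | 63% | 56% |
| 2 | 1.43 | 0.5% | 50% | 39% |

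The last column takes one reading of the Bonferroni rule (six time points) and a load effect of 1.155 SD, again 80% with sex modelled. At 8 per cell and alpha 0.05, pooled power at gaps of 0.5, 1, 1.5 and 2 SD is 78%, 72%, 62% and 49%.

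**4. If the coin toss is taken literally.** The chance of an exact 10/10 split is C(20,10)/2²⁰ = 0.176 in one sex and 0.176² = 0.031 in both. Simulated with a plain coin toss (8,000 trials), the pooled t test has a type I error of about 5%, so it is no longer conservative on average. The power loss remains: 69% against 78% with sex modelled at a 1 SD gap, and 49% against 77% at 2 SD.

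**5. Load-by-time interaction of the mixed ANOVA** (5,000 trials, six time points, assumed within-subject correlation 0.5). A sex gap that is constant over time cancels: power is about 77% with or without sex. A sex difference that changes over time does not cancel: power without sex against with sex is 73% against 78% at 1 SD, 65% against 76% at 1.5 SD and 55% against 76% at 2 SD.

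**The case against.** The strongest reply is that A62 already plans a load-by-sex ANOVA for each marker. With equal cells, its load effect is the mean of the male and female load differences on within-cell error, which is the sex-adjusted contrast. A reader might infer that no Part A load comparison accounts for sex; A62 does not support that. But this ANOVA has no time factor, and the comparisons at each time point go to the unadjusted t tests.

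A second reply is that the outcome is change (A57), and a stable sex gap cancels from change scores just as it does from the load-by-time interaction. That also stands. It would be wrong to say that every marker differing by sex loses power in every test. Strength is the obvious candidate for a large but stable gap, and A60 frames it as a percentage difference. However, A62 does not say that the t tests use changes, and the larger and longer-lasting rise in men that A12 describes is a sex difference that varies over time, which does not cancel.

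A third reply is that balance on sex is an intention in A13 that the coin toss in A61 does not secure. The claim that the test is conservative therefore holds only if balance is achieved. The loss of power does not depend on it.

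Finally, this is a matter of efficiency, and the gap sizes are assumed. Both points are fair. The choice of tests is nevertheless written into A62, so it is not simply left open for a later analysis plan.

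**Conclusion.** The point holds as a loss of precision in the time-specific load comparisons. For the pooled t tests it costs about 2 percentage points of power at a 0.5 SD sex gap, 7 at 1 SD, 17 at 1.5 SD and 30 at 2 SD, and essentially nothing at 0.2 SD or less. These figures rest on an assumed gap, normal data with a common SD, and a load effect set to give 80% power with sex modelled. For the load-by-time interaction the cost arises only from a sex difference that changes over time, and its size also depends on the assumed within-subject correlation.

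A reader might infer that the load comparison is biased or invalid. The documents do not support that: the type I error is at or below about 5% whether the sexes are balanced as intended or allocated by a plain coin toss. The change is worth making because it is nearly free and lets the analysis use a factor that the design intends to balance.

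**What to change.** In A62 Part A, replace the two separate two-way ANOVAs with one mixed model containing load, sex and time and their interactions. Take the load comparison at each time point from that model as the mean of the male and female load differences, in place of the pooled independent t test, and keep the Bonferroni correction.

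The cost is one line of text and two error degrees of freedom per time-point comparison (with 40 people, 36 instead of 38), with no extra data or participants. If a marker has no sex gap, power is essentially unchanged. If allocation leaves the sexes unequal across loads, the same contrast still compares loads within sex.

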**A57. What is the primary outcome measure for the study?**

Exercise-induced changes in markers of muscle damage

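### The time-point comparisons between groups in A62 (both parts) are not adjusted for the pre-exercise value, although it is collected for every marker; adjusting would be a free improvement

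*Protocol*

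**What the plan says.** - A57 gives the primary outcome as "Exercise-induced changes in markers of muscle damage".
- A62, Part B, sets out the repeated-measures analysis: "A two-way mixed design ANOVA will be used to analyse each muscle damage marker between dietary conditions" and across time points. For the group comparison at individual times it adds: "Independent t tests with Bonferroni corrections will be used to compare time-points between dietary conditions for all measures". Within-group changes go to paired t-tests.
- A62, Part A, has the same structure with exercise load in place of diet, and adds a two-way between-subjects ANOVA of load by sex. No analysis in either part names a baseline covariate.
- A13 shows that the baseline exists. Blood markers, thigh circumference, range of motion, VAS soreness and pressure-pain threshold are all taken at visit 3 before the bout. 1RM is tested at visits 1 and 2, about three weeks earlier, and again at visits 6 and 7.
- A60 sizes Part B at 9 per group for "80% power to detect a between-group difference in muscle strength of 13" per cent, "when using a dependent t-test" and "with a 0.05 two-sided significance level". It adds that "A ~20% drop-out is anticipated" and recruits 22. Part A recruits 10 per sex-by-load cell, which is 20 per load.

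**The concern.** The question is about change, and each participant supplies a starting value, but the tests that give the group difference at each time are not specified to use it. If they run on the values at that time, stable between-person variation stays in the error term. Chance baseline imbalance then carries into the estimate in proportion to the pre-post correlation. In Part B such imbalance is not rare. The difference between two baseline means has standard error sqrt(2/n) SD, which is 0.471 at n = 9 and 0.426 at n = 11. A gap above 0.5 SD therefore occurs with probability of about 29% and 24%. Because A62 names the method, this is not a detail left open for a later analysis plan.

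**Working it through.** **Inputs.** From A60: two-sided alpha 0.05, 80% power, a 13% difference and 9 per group (Part B). Assumed, because the protocol does not give it: the pre-post correlation rho, shown from 0.1 to 0.8.

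**The plan's own figure.** The 9 per group cannot be reproduced, because no SD is given (nor a correlation, for the dependent test). Solving backwards with the non-central t distribution, 9 per group and 80% power imply d = 1.407 for an independent t-test, so SD = 13/1.407 = 9.24 points. For a dependent t-test they imply 1.067 SDs of the paired difference, so SD = 13/1.067 = 12.2 points. I use d = 1.407 as the benchmark. It starts the unadjusted test at the planned 80% and keeps the choice of a dependent t-test, a separate matter, out of the comparison.

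**Variance relative to a t-test on post values.**
- Change score: 2(1 − rho).
- ANCOVA: (1 − rho²) × [1 + 1/(2n − 4)]. The bracket is the cost of estimating the covariate slope, and one further degree of freedom is lost.
- At n = 9, rho = 0.5: 0.75 × (1 + 1/14) = 0.804. At rho = 0.7: 0.51 × 1.0714 = 0.546.

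**Power.** Non-centrality is d × sqrt(n/2) / sqrt(variance factor). Degrees of freedom are 2n − 2 for the t-tests and 2n − 3 for ANCOVA.

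| rho (assumed) | Post-value t-test, n = 9 | Change-score t-test, n = 9 | ANCOVA, n = 9 | ANCOVA, n = 11 (unadjusted 88.1%) |
|---|---|---|---|---|
| 0.1 | 80.0% | 55.2% | 77.3% | 86.5% |
| 0.3 | 80.0% | 65.9% | 80.6% | 89.1% |
| 0.5 | 80.0% | 80.0% | 87.5% | 94.0% |
| 0.7 | 80.0% | 95.1% | 96.5% | 98.9% |
| 0.8 | 80.0% | 99.3% | 99.4% | 99.9% |

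At a Bonferroni level of 0.05/6 (the number of comparisons is assumed) and n = 9, unadjusted power is 50.9%. ANCOVA gives 51.4%, 61.9% and 82.2% at rho 0.3, 0.5 and 0.7.

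**The mixed ANOVA.** I simulated 4,000 trials per setting with 9 per group, one pre and five post times, compound symmetry and a constant post-exercise effect of about 1.4 SD. At rho 0.3, 0.5 and 0.7 the group-by-time test had power of about 68%, 84% and 98%. ANCOVA at one time had about 81%, 88% and 97%. The interaction is weaker at low correlation and level at 0.7.

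**Missed visits.** Pre and post both fall on visit 3, the exercise day, so only visits 4 to 7 can be missed afterwards. If 3% or 5% of those are missed at random (assumption), 0.97⁴ = 89% or 0.95⁴ = 81% of participants have every time point.

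**What the Part B pre value measures.** A13 describes a breakfast dose three hours before the visit, one dose after exercise and two at home. The count of 4 × 4 + 1 = 17 doses works only if visit 3 includes the breakfast dose. The visit 3 value therefore follows the first supplement dose. Visit 2 1RM does not, since it precedes randomisation.

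**The case against.** The strongest reply is that the mixed ANOVA, with pre as a level of time, already compares changes. Its group-by-time test removes stable between-person differences and fits the wording of A57. That stands, and it confines the loss mainly to the time-point t-tests and Part A's load-by-sex ANOVA.

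Several stronger readings are tempting but not supported:

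- **That the t-tests use raw values.** A62 does not say whether values or changes are compared. If changes were meant, ANCOVA still has (1 + rho)/2 of the change-score variance before its small covariate cost, so the advice is unchanged.
- **That a complete-case analysis is planned.** A62 gives no missing-data rule, and silence on this is not a finding here. It is fair only to say that a classical repeated-measures ANOVA ordinarily drops anyone with a missing time, and that a mixed model does not. At the rates assumed above the loss is within the drop-out allowance in A60.
- **That planned power is really about 57% and adjustment rescues it.** That start reuses the dependent-test effect size (1.067) as an independent-groups d. It reflects the sizing test, not the missing covariate.
- **That every comparison rests on 8 to 11 per group.** Part A's load comparison has 20 per condition, or 16 after 20% drop-out (40 × 0.8 / 2). Only its sex-by-load cells are that small.

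It is also true that the gain can vanish: at rho 0.1 adjustment costs about 3 points of power at 9 per group. For 1RM the baseline is about three weeks old, which may lower rho. A fully unstructured covariance over five post times has 5 × 6/2 = 15 parameters, for about 18 Part B completers, and may not converge.

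**Conclusion.** The point holds as a free improvement rather than an error that invalidates the analysis. In both parts, the group comparisons at individual times, and Part A's load-by-sex ANOVA, carry no adjustment for a pre-exercise value that is collected anyway. Using it protects small groups against chance imbalance. At 9 per group and d = 1.41 it moves power from 80% to about 77%, 81%, 88% and 97% at rho 0.1, 0.3, 0.5 and 0.7. These figures rest on an undocumented rho, on a benchmark effect back-solved from A60, and on t-tests of post values. They illustrate Part B; Part A's load comparison has larger groups.

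**What to change.** In A62, both parts, replace the time-point t-tests with baseline-adjusted group contrasts. These can come from an ANCOVA at each time or from one linear mixed model per marker on the post-exercise times. Specify:

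- group, time, group × time and the pre-exercise value as covariate (log scale for blood markers; visit 2 value for 1RM);
- in Part A, also sex and sex × load, which brings the load-by-sex question into the same adjusted model;
- small-sample degrees of freedom, and a named parsimonious covariance as fallback if unstructured does not converge;
- the multiplicity correction, kept as now.

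The mixed model also retains participants who miss a visit. In Part B, state that the visit 3 covariate is pre-exercise but not pre-supplement, because any effect of the first dose on it would be adjusted away.

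The cost is new wording in A62 and slightly more analysis work. No extra data, visits or participants are needed.

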#### A64. Details of research sponsor(s)

##### A64-1. Sponsor

###### Lead Sponsor

Status: ☐ NHS or HSC care organisation

☒ Academic

☐ Pharmaceutical industry

☐ Medical device industry

☐ Local Authority

☐ Other social care provider (including voluntary sector or private organisation)

☐ Other

*If Other, please specify:*

Commercial status: Non-Commercial

